### Intervention measures

All participants will be randomly assigned to one of two groups, receiving treatment three times per week for a duration of 6 weeks. All treatments will be administered by therapists with over 10 years of clinical experience. The therapists must have undergone specialized training in CSE and passed clinical assessments to ensure consistency in the treatment provided to all patients. Building on previous studies, the therapists will demonstrate and explain a modified CSE training program to the participants in both groups (Table 1) [19]. The progression of CSE detailed in Table 1 represents a general framework for advancing exercise difficulty over the 6-week intervention period. The duration and structure of the CSE program were designed based on evidence from previous studies indicating the efficacy of similar protocols in patients with NSLBP [5,11,20]. However, we acknowledge that not all patients may progress at the same rate due to variability in pain levels, functional capacity, or motor control impairments. To accommodate individual differences, the exercise progression will be tailored to each patient’s abilities and clinical presentation. The supervising therapist will evaluate the patient’s pain, functional status, and motor performance at each session. Progression to subsequent levels will only occur when the patient demonstrates: Adequate pain tolerance during the current exercise level (i.e., no significant exacerbation of symptoms). Sufficient motor control and stability to safely perform the next level of exercises without compensatory movement patterns. During the treatment and observation periods of the study, if a participant’s pain symptoms worsen, they will be instructed to take NSAIDs, specifically celecoxib (Pfizer Pharmaceuticals Ltd.), at a dose of 200 mg twice daily for two consecutive days. If the pain does not subside, the participant will be withdrawn from the study.

**Table 1 pone.0322398.t001:** Core stability exercise.

Week 1–2	Week 3–4	Week 5–6
Supine Transverse Abdominis Contraction Training: Move the belly button towards the spine.	Supine Transverse Abdominis Contraction with Opposite Arm and Leg Lift (Not Touching the Ground).	Supine Transverse Abdominis Contraction with Double Leg Bridge.
Supine Transverse Abdominis Contraction with Heel Slide.	Supine Transverse Abdominis Contraction with Double Leg Bridge.	Supine Transverse Abdominis Contraction with Air Cycling Movement.
Supine Transverse Abdominis Contraction with Lower Limb Lift.	Supine Transverse Abdominis Contraction with Single Leg Bridge (Left Leg).	Supine Transverse Abdominis Contraction with Crunch (Hands Touching Knees).
Supine Transverse Abdominis Contraction with Contralateral Limb Elevation.	Supine Transverse Abdominis Contraction with Single Bridge (Right Leg).	Kneeling Hand-Knee Position with Transverse Abdominis Contraction While Raising the Opposite Upper and Lower Limbs.
Supine Transverse Abdominis Contraction with Double Leg Bridge.	Kneeling side bridge (left side).	Kneeling side bridge with knee extended (left side).
Kneeling Hand-Knee Position with Transverse Abdominis Contraction While Raising the Upper Limb.	Kneeling side bridge (right side).	Kneeling side bridge with knee extended (right side).
Kneeling Hand-Knee Position with Transverse Abdominis Contraction While Raising the Lower Limb.	Prone position transverse abdominal contraction with opposite limb raise.	Prone position transverse abdominal contraction with opposite limb raise.
Kneeling Hand-Knee Position with Transverse Abdominis Contraction While Simultaneously Raising the Contralateral Upper and Lower Limbs.	Kneeling Hand-Knee Position with Transverse Abdominis Contraction While Simultaneously Raising the Contralateral Upper and Lower Limbs.	Plank Exercise

Participants in the experimental group will receive NMES using the EN-Stim4 device (ENRAF-NONIUS B.V., Bunnik, Netherlands) applied to the bilateral LM and TrA/internal oblique muscles(IO) (Fig 3). For the NMES configuration, the abdominal electrodes will be positioned as follows: the cathode (negative electrode) will be placed 1 cm above the iliac crest along the mid-axillary line, while the anode (positive electrode) will be located 2 cm medial to the anterior superior iliac spine. For the lumbar electrodes, the cathode (negative electrode) will be positioned approximately 2 cm lateral to the spinous processes of L4 and L5, with the anode (positive electrode) placed at a distance from the cathode to ensure optimal current flow through the lumbar region [21]. The electrodes used will be 5 cm × 5 cm surface hydrogel electrodes. The NMES used in this study will be applied with the following parameters: a frequency of 50 Hz, a 200 μs pulse width, and a biphasic symmetric waveform, which is effective for recruiting both superficial and deep muscle fibers [22]. The stimulation will follow a contraction-relaxation cycle comprising an ascent phase of 1 second, a contraction phase of 4 seconds, a descent phase of 1 second, and a resting phase of 6 seconds, lasting a total of 20 minutes. The current intensity will be adjusted to achieve the maximum muscle contraction without causing discomfort, such as burning sensations or severe cramping pain. NMES intensity is adjusted weekly based on participant feedback and tolerability, as well as to match improvements in muscle strength and activation capacity. Intensity increases are guided by the participant’s perception of a “strong but comfortable” stimulation level and monitored through visible muscle contractions. CSE will be performed during the contraction phase of the electrical stimulation and will cease during the resting phase. These exercises will include abdominal activation training in supine, prone, and quadruped positions, as well as bridge exercises and planks (Table 1). Each session will consist of 8 different exercises, performing 1 set of 10 repetitions per exercise, lasting 20 minutes per session, once per day, 3 days per week [23]. Participants in the control group will undergo the same CSE and NMES treatment, but the NMES current intensity will be set to a level that only elicits minimal sensory perception in the participants (generally below 5 mA). This ensures that while the participants experience the same treatment protocol, they do not receive the therapeutic benefits of NMES, allowing for an effective comparison between the experimental and control groups.

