## Methods

### Study design

This study will be a single-center, prospective, randomized, sham-controlled trial conducted at the outpatient rehabilitation center of the Sir Run Run Shaw Hospital, affiliated with Zhejiang University School of Medicine. A total of 52 participants will be recruited and randomly assigned in a 1:1 ratio to one of the following two groups: (a) experimental group, receiving NMES superimposed on CSE to enhance activity levels; (b) control group, receiving the same CSE with sham NMES. All participants in both groups will undergo 20-minute sessions, three times per week, for a 6-week intervention period. The study outcomes will be evaluated before (t0), six weeks after initiating interventions(t1), and six months (t2) after starting the protocol. The study protocol follows the standards described in the “Standard Protocol Items: Recommendations for Interventional Trials” guideline (S1 File) [12].

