### Sample size calculation

The sample size for this study is determined based on previous findings reported by Songjaroen et al [17]. The test statistic used to calculate the sample size was based on a mixed ANOVA. The calculation is based on the anticipated effect size for LM activation improvement, with a large effect size (Cohen’s dz = 0.7), a statistical power of 80%, a significance level of 5%, and a standard deviation of 0.05 points. Using G*Power 3.1 software for the analysis, it is calculated that at least 43 participants are required. Considering an anticipated dropout rate of 20%, a total of 52 participants will be recruited for the study (26 in the experimental group and 26 in the control group).

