### Randomization and blinding

After participants are enrolled in the study and have completed baseline assessments, an independent technician will generate a randomization sequence. The random sequence will be created using a random number generator (IBM SPSS Statistics V.25.0 software; IBM). The random allocation sequence will be sent to the therapists in sequentially numbered opaque envelopes [18]. The therapists will open the envelopes in sequence and assign participants, who meet the inclusion criteria, to the corresponding group. While the study assessors will be blinded to the group allocation of the participants, neither the therapists nor the participants can be blinded due to the nature of the interventions. The continued use of sham NMES for participants can play a key role in minimizing performance bias. Sham NMES provides a control condition that mimics the setup and experience of the intervention without delivering therapeutic electrical stimulation. This approach enables us to isolate the effects of active NMES on clinical outcomes (such as pain, proprioception, and muscle activation) by ensuring that any observed improvements are not simply due to placebo effects, psychological factors, or participants’ awareness of receiving NMES treatment. To minimize bias, assessors, data managers, and analysts will remain blinded to group assignments during outcome assessments and data analysis. The study design and trial flowchart are illustrated in Figs 1 and 2.

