### Strategies to increase treatment adherence

Assessors will maintain regular communication with participants throughout the study to monitor their progress and address any discomfort or challenges. Participants will be encouraged to promptly report any increase in pain, discomfort, or difficulty in performing exercises or tolerating NMES. If any issues arise, the research team will assess the individual’s condition and make necessary adjustments to the treatment protocol. These adjustments may include modifying the intensity or duration of NMES, altering the difficulty level of exercises, or providing alternative movements to ensure proper execution while minimizing pain. If NMES settings prove intolerable, parameters such as frequency, intensity, or pulse duration may be adjusted to improve comfort without compromising effectiveness. Additionally, the progression of CSE will be personalized, allowing flexibility in exercise advancement based on each participant’s physical capability. To enhance adherence, assessors will offer continuous guidance, encouragement, and regular check-ins, reinforcing motivation and addressing concerns in real time. By implementing these strategies, the study aims to optimize participant engagement, ensure a tolerable and effective intervention, and maximize the benefits of the treatment protocol.

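### The pain rule takes participants out of the study, not just off treatment, and still applies after treatment has ended, so outcomes are lost because pain went badly

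*Protocol article*

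**What the plan says.** The rule stands in the protocol article under Intervention measures. Its scope is "During the treatment and observation periods of the study". A participant whose pain worsens takes celecoxib 200 mg twice daily for two days. Then: "If the pain does not subside, the participant will be withdrawn from the study".

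The timing comes from Study design. Sessions run "three times per week, for a 6-week intervention period", t1 is at six weeks, and the last assessment is "six months (t2) after starting the protocol".

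Four other places bear on the point:
- Secondary outcome measures lists pain on the VAS (0 to 10) and disability on the ODI.
- Strategies to increase treatment adherence answers rising pain by "modifying the intensity or duration of NMES, altering the difficulty level of exercises", among other adjustments.
- Data collection and management provides telephone contact so that follow-up assessments are completed. It does not mention participants who have been withdrawn.
- Sample size calculation sets the total of 52 with the words "Considering an anticipated dropout rate of 20" per cent.

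**The concern.** The rule joins two decisions that should be separate: stopping treatment and leaving the study. During the six treatment weeks, safety can justify the first. After week 6 there is nothing left to stop, and a flare can be treated without ending participation, so all the rule can do is end data collection.

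Its trigger is worsening pain, which is itself an outcome. The missing values are therefore created by the protocol and depend on the result. Those who remain look better than the arm as randomised. If NMES reduces pain, fewer of its participants meet the trigger, so more of the poor results are removed from the control arm and the comparison narrows. The dropout allowance replaces lost numbers but does not correct selection on outcome. An analysis plan can choose an estimator, but it cannot recover values that were never collected.

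**Working it through.** **1. How long the rule runs with no treatment to stop.** Six months is about 26 weeks and treatment lasts 6, so 26 - 6 = 20 weeks.

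**2. Which assessments are lost.** Withdrawal before week 6 loses t1 and t2. Withdrawal after week 6 normally loses t2 only, so the six-week comparison is untouched by later withdrawals.

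**3. Direction and size.** The plan gives no figure to reproduce, so this is an illustration in which every input is assumed. Lower scores are better.
- VAS change has SD 2.0, with true mean mu = -1 (control) and -2 (NMES), a true difference of 1.0.
- The flare X and the visit change Y have the same mean and SD, with correlation r = 0.5 to 1.0.
- A participant worsens if X > c, with c = 0.5 to 1.5 points. A share f of those who worsen fails rescue and is withdrawn.
- One time point is modelled.

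Formulas, per arm:
- z = (c - mu)/SD; P = P(X > c); withdrawn share w = f × P
- mean Y among the worsened: m = mu + r × SD × phi(z)/P
- mean Y among those remaining: (mu - w × m)/(1 - w)

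Worked case, f = 0.25, c = 0.5, r = 1:
- Control: z = 0.75, P = 0.2266, phi = 0.3011, w = 0.0567, m = -1 + 2 × 0.3011/0.2266 = 1.658. Remaining mean (-1 - 0.0567 × 1.658)/0.9433 = -1.160.
- NMES: z = 1.25, P = 0.1056, phi = 0.1826, w = 0.0264, m = -2 + 2 × 0.1826/0.1056 = 1.458. Remaining mean (-2 - 0.0264 × 1.458)/0.9736 = -2.094.
- Difference: 2.094 - 1.160 = 0.934, a shrinkage of 6.6%.

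Over all c and r in the ranges above:

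| f | Withdrawn, control | Withdrawn, NMES | Of 52 | Control mean remaining (true -1.0) | Difference (true 1.0) | Shrinkage |
|---|---|---|---|---|---|---|
| 0.10 | 1.1-2.3% | 0.4-1.1% | under 1 | -1.02 to -1.06 | 0.990-0.975 | 1-2.5% |
| 0.25 | 2.6-5.7% | 1.0-2.6% | 1-2 | -1.05 to -1.16 | 0.975-0.934 | 2.5-6.6% |
| 0.50 | 5.3-11.3% | 2.0-5.3% | 2-4 | -1.10 to -1.34 | 0.948-0.853 | 5-15% |
| 1.00 (upper bound) | 10.6-22.7% | 4.0-10.6% | 4-9 | -1.20 to -1.78 | 0.886-0.630 | 11-37% |

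**4. When the bias is zero, and when its sign can change.** With equal means, SDs and application in both arms, the between-arm bias is 0. With both means at -1 but SD 2.0 in one arm and 1.5 or 2.5 in the other, the same formulas at f = 0.5 give a false difference of 0.06 to 0.14 VAS points. Its sign depends on which arm has the larger spread.

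**5. Primary outcomes.** The shift in an sEMG measure, in SD units, is f × rho × phi(z)/(1 - w) per arm, where rho is the assumed flare-to-sEMG correlation. With f = 0.5, c = 0.5 and rho = 0.3, control is 0.5 × 0.3 × 0.3011/0.8867 = 0.051 and NMES is 0.5 × 0.3 × 0.1826/0.9472 = 0.029, a difference of 0.022 SD. Over c = 0.5 to 1.5 and rho = 0.15 to 0.3, the range is 0.008 to 0.022 SD at f = 0.5, and 0.017 to 0.056 SD if all fail rescue.

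**The case against.** **The article never says that assessments stop.** It is a condensed report, its flow diagram is not shown, and the handling of withdrawn participants is often left to a fuller document. This lowers confidence. It does not remove the point, because the stated rule is withdrawal from the study, and a treatment-only reading has no content once treatment is over. If continued follow-up is intended, the sentence still needs correcting.

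**Therapists as judges of withdrawal.** A reader might infer that unblinded therapists decide who is withdrawn, since they evaluate "pain, functional status, and motor performance at each session". The documents do not support this. That evaluation governs progression through the exercises, nothing names the therapist as judge of withdrawal, and there are no sessions after week 6. What stands is narrower. The article says "neither the therapists nor the participants can be blinded due to the nature of the interventions", so participants' own reports of worsening could differ by arm.

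**Size.** A reader might also fasten on the 37% shrinkage. It needs every worsened participant to fail rescue, the lowest threshold, and a flare identical to the visit score. Nothing in the article supports a failure share of half or more, and adjusting the treatment should make failure rarer during the first six weeks. With SD 2.0 and 26 per arm, the standard error of the VAS difference is 2 × sqrt(2/26) = 0.55 points, well above the 0.05 to 0.15 lost when half fail. This objection stands as a limit on weight.

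**Safety.** Stopping NMES or exercise for uncontrolled pain is right, and some of these participants could not do the 5 kg lift. Neither prevents completing a VAS and an ODI.

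**Conclusion.** The point holds as a badly fixed conduct rule. The protocol ends study participation on the basis of an outcome, and for about 20 of 26 weeks this serves no treatment-stopping purpose. The loss is t1 and t2 for withdrawals during treatment and normally t2 alone afterwards.

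The within-arm improvement is overstated. The between-arm VAS difference is attenuated if NMES works, and can move in either direction if withdrawal or spread differs by arm. The true size cannot be derived from the article. A few per cent is plausible if a minority of worsened participants fail rescue, and 5-15% if half do. Both figures rest wholly on the assumed SD, means, thresholds and correlations.

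A reader might infer that the rule threatens the primary result or manufactures a benefit. Neither follows: the sEMG effect is small under these assumptions, and a false benefit needs unequal spread or unequal application, which the article does not show. The change is worth making because it is cheap and the lost values could not be recovered later, but the stakes lie mainly in VAS and ODI at six months. Confidence is medium, given the silence on what happens to withdrawn participants.

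**What to change.** Replace the withdrawal sentence with:

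> *If the pain does not subside, the study intervention will be discontinued (if still ongoing) and the participant managed clinically; unless consent is withdrawn, the scheduled t1 and t2 assessments will still be done.*

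Add that VAS and ODI are the minimum at those visits and that physical tests are done only if clinically suitable. Keep these participants in their randomised arm. Record rescue use and pain-related discontinuation, and report both by arm.

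The cost is this sentence, a line in the consent form, and follow-up of a few more participants: about 2 to 4 of 52 if half fail rescue, fewer at lower shares, and up to 9 as an upper bound. Telephone contact for follow-up is already planned. Some of these participants will have no physical tests, so the gain is mainly in VAS and ODI. The comparison then estimates the effect of assignment, including rescue and stopping.

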
**Fig 3 pone.0322398.g003:**
[figure not shown]
Examples of NMES superimposed on CSE: A) Quadruped position with transverse abdominal contraction while simultaneously raising the contralateral upper and lower limbs; B) Supine position with transverse abdominal contraction accompanied by a double bridge.

### Primary outcome measures

Surface Electromyography (sEMG) Muscle Activity: Muscle activity will be recorded using the MegaWin ME6000-T8 surface electromyography system (Finland). The system will be set to manual recording mode, utilizing low-pass bipolar analog signals with a 32-bit microcomputer. The instrument sensitivity will be set to 1 µV, with a filtering range of 8–500 Hz and a sampling frequency of 1000 Hz. The measurements will be conducted using a differential preamplifier and a free raw data measurement method. Standardized disposable electrodes will be used to eliminate the possibility of reuse. The connection of the electrodes to the electromyography device will be adjusted to ensure that it does not impede the participants’ movements and to prevent the disconnection of the surface electrodes or data line connectors due to tension. The electrode spacing will be set to 2.5 cm and positioned parallel to the muscle fibers of the following muscles: external oblique(EO) (approximately 15 cm lateral to the umbilicus), TrA/IO (2 cm superior and medial to the anterior superior iliac spine), erector spinae(ES) (2 cm lateral to the spinous processes of L1), LM (2 cm lateral to the spinous processes of L5), and anterior deltoid (two fingerbreadths from the anterior aspect of the acromion) [24]. All electrodes will be placed on the more severely affected side of NSLBP patients. The reference electrode will be connected to the iliac crest. The EMG data will be measured for 5 seconds. After excluding the first and last second, the root mean square (RMS) values of the 3 seconds of sEMG signal will be calculated [25].

Measurement of Muscle Activation Timing: To assess the latency of trunk muscle activation, participants will perform a lifting task while standing quietly, which introduces an inherent perturbation to the trunk and requires anticipatory postural adjustments (APA) [24]. The electrode placements will be the same as those used for muscle activity monitoring. Participants will stand with their elbows fully extended at 0°, shoulders flexed at 40°, and grasp the handles of a 5 kg box placed on a table in front of them. They will be instructed to lift the box to a shoulder flexion angle of 90° as quickly as possible and maintain this position for 3 seconds. After familiarizing themselves with the movement, participants will complete three repetitions of the lifting task, with a 1-minute interval between each trial. If any trunk or pelvic motion is observed during the trial, that attempt will be considered a failure. For sEMG processing, the procedures for manually selecting activation timings are as follows: Raw sEMG signals will first be filtered using a band-pass filter (20–450 Hz) to remove noise and artifacts. The baseline sEMG levels will be defined by calculating the RMS value of a 500 ms resting period before the onset of muscle activation. Muscle activation will be identified when the sEMG signal exceeds 3 standard deviations (SD) above the baseline RMS for a minimum duration of 50 ms. If necessary, trained assessors will visually inspect and manually adjust the activation timing to account for signal variations and artifacts, ensuring consistency across trials. The relative difference in onset activation times between each trunk muscle and the anterior deltoid will be calculated using the following formula: Relative Onset Activation Time Difference = Onset Activation Time of Trunk Muscle - Onset Activation Time of Anterior Deltoid (ms) [26]. A positive value indicates that the target trunk muscle is activated after the anterior deltoid. The average onset time from the three repetitions for each trunk muscle will be computed and used as the basis for data analysis.

